#### *Potential predictors*

##### Variables measured T0

- Adverse event (AE)/serious adverse event (SAE)
- Physical parameters: BMI, lean body mass
- Heart Rhythm
- Forced expiratory volume (FEV)1 L\*min
- Lab (LDL, HDL, Total cholesterol, Triglyceride, HbA1C, Creatinine, CRP, Hb)
- Physical activity prior to index event
- Symptoms (CCS & NYHA class)
- Medication use

##### Variables measured at T1

- AE/SAE
- Drop-out mCR programme
- Reason drop-out of CR programme
- Drop-out study
- Reason drop-out of study
- Attendance to multidisciplinary sessions
- Medication use

Additionally the following analyses will be considered:

- Structural Equation Models (to explain satisfaction and fulfilment of expectations)
- Cluster Analysis (to identify and characterize different profiles of users and link them to the program adherence)

[figure not shown]

## 14. Safety

The safety population will be used to describe the safety. Safety data will be coded according to MedDRA PT and will be summarised in tables by intervention group, centre and overall.

### *Adverse events*

Deaths and SAEs will be listed on patient level by intervention group.

When calculating the incidence of AEs, or any sub classification thereof by intervention, time period, severity, etc. each subject will only be counted once and any repetitions of AEs will be ignored; the denominator will be the total population size.

[figure not shown]

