**Objectives:** 1. To assess whether mobile telemonitoring guided CR (*mCR*) programmes result in better sustained effects on physical, mental and social outcomes in elderly patients not opting for regular CR, than patients who do not follow the *mCR* programme. 2. To assess whether *mCR* as alternative for a regular CR programme is an effective means to increase participation and adherence of elderly in a CR programme. 3. To analyse the induced costs of the *mCR* programme and determine its cost effectiveness.

**Study design:** Randomised controlled trial

**Study Centres and Geography:** 6 centres in several European countries

**Study population:** Elderly cardiac patients who are indicated for CR but not opting for regular CR

**Sample size calculation:** 238 patients in total (119 per study arm) divided over 6 centres, indicating approximately 40 patients per centre.

**Intervention:** Patients aged 65 years and older, who are candidate for CR, but not opting for regular CR are randomised in two study arms: the *mCR* programme for 6 months or no *mCR* programme. The *mCR* programme involves a home-based programme for 6 months in which patients are supplied with a smartphone/application with a data subscription from MobiHealth. Through this application patients are able to measure and register physical activity, heart frequency and intensity (BORG scale) and can monitor progress. Patients are instructed to perform a moderate exercise 5 days per week for at least half an hour. A care professional (typically a CR nurse) also has access to a portal to monitor progress of different patients, advice on rehabilitation approach and stimulate compliance telephone calls. During the first month patients receive weekly individual coaching and feedback on their results by telephone, in the second month this will be once per two weeks, whereas one monthly call will be held in the last four months (month 3 until 6) of the mobile telemonitoring period. In the second period without mobile telemonitoring (month 7 until 12) patients will receive no coaching or feedback by phone. Patients participating in the control group with no *mCR* programme receive no advice or coaching throughout the study period.

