### 7.5 Randomisation, blinding and treatment allocation

At the start of the CR programme, once patients have indicated not to be interested in the regular CR programme, patients will be informed about the study and requested to participate. After receiving written consent from the patient they will be randomised in 1:1 ratio to the intervention group with mobile telemonitoring guidance or the control group with no mobile telemonitoring guidance or other CR programme by means of computerised allocation system applying an algorithm that prevents the care providers or the investigators from predicting the outcome of the randomisation

process. This means that the person, who determines if the patient is eligible, at the time of this decision, is unaware of which group the patient will be allocated to. The patient, care provider and outcome assessor will not be blinded to the intervention itself because of safety concerns.

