### 3. Sample size

In order to assess the effects on sustained physical fitness after participation in the *mCR* programme it was determined that an inclusion of 119 patients per group would be sufficient to examine the aim of this study. This is based on the expected difference in increase in  $VO_{2peak}$  level of 3.0 ml/kg/min at 6 months between the control and intervention group with an estimated standard deviation of 5 ml/kg/min in the intervention group and 6 ml/kg/min in the control group. Assuming 80% power and 5% two-sided significance level ( $\alpha=0.05$ ), the sample size ( $n$ ) required to achieve a probability of 80% of detecting a difference in an increase  $VO_{2peak}$  level between two independent groups is  $n=55$  per randomisation group. Since patients from different centres (countries) will be pooled in the analysis, we will apply an adjustment for dependency of the observations to calculate the sample size, based on an estimated intraclass correlation coefficient (ICC) for the study centres. The ICC is the proportion of the total variance which is between the centers rather than within centres. An ICC of 0.05 is used in the sample size calculations. After adjustment for the ICC the sample size is  $N=83$  per group. Based on 30% withdrawal we aim for a group size of  $n=119$  per randomisation group ( $n=238$  in total). Six centres will participate in the RCT so we will aim at including approximately 40 patients per centre. As this is a cooperative trial, centres may recruit more patients than this recruitment goal. When one centre starts to dominate enrolment however, recruitment might need to be capped. The total sample size ( $n=238$ ) would be sufficient to detect a clinically and physiologically relevant change in peak oxygen consumption, despite a 30% dropout.

[figure not shown]

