#### **4.2.1 Full analysis population**

The main outcome analyses will be based on the full analysis population. The full analysis population consists of all randomised subjects who signed informed consent. Subjects will be analysed according to the intervention group they were randomised to (intention to treat), irrespective whether the subjects complied to the use of the smartphone according to protocol.

[figure not shown]

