#### **4.2.3 Safety population**

The safety population is equal to the full analysis population (section 4.2.1).

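### SAP section 14 sets one AE denominator, the total population: read literally it shrinks arm and centre rates, and on either reading it is wrong for time-period splits

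*Combined protocol and SAP*

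**What the plan says.** SAP section 14 gives one counting rule. Its scope is wide: "When calculating the incidence of AEs, or any sub classification thereof by intervention, time period, severity, etc". Within that scope each subject counts once, and "any repetitions of AEs will be ignored; the denominator will be the total population size". The opening of the same section adds that safety data "will be summarised in tables by intervention group, centre and overall". Centre is not named in the denominator sentence; it enters through this table specification.

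The population is defined in SAP section 4.2: "The safety population is equal to the full analysis population", and "The full analysis population consists of all randomised subjects who signed informed consent". Withdrawn patients therefore stay in it. The protocol summary plans "238 patients in total (119 per study arm) divided over 6 centres, indicating approximately 40 patients per centre", and protocol section 7.5 says of patients that "they will be randomised in 1:1 ratio to the intervention group" or to control. On withdrawal, SAP section 3 states "Based on 30% withdrawal we aim for a group size of" 119; no split by arm is given.

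Two other provisions decide who can contribute an AE. SAP section 4.7 uses a discontinuing patient's data only up to discontinuation. Protocol section 7.10 follows patients who leave the study for a short list of major outcomes and for use of care; general AEs are not on that list. Neither document gives an at-risk denominator, a person-time denominator or an exposure-adjusted rate for AEs.

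**The concern.** An incidence is interpretable only if its denominator is the set of people who could have entered the numerator. The rule in section 14 can fail this in two separate ways.

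- **Whose total?** If it means the whole safety population, an arm's count is divided by both arms and a centre's count by all six centres.
- **At risk when?** Even if it means the arm's total, a later period is divided by patients who left before it began.

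The first affects the size of the reported rates. The second can affect the comparison between arms, because this is an open trial against no programme and withdrawal may well differ by arm. Analyses are shared among several beneficiaries and the CRO (SAP section 16), so an undefined denominator could also be implemented differently by different analysts. Because repeat events are ignored and no event count is specified, a patient with recurrent events looks the same in the tables as a patient with one.

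**Working it through.** **Plan's own figures.** 83 per group after the ICC adjustment, inflated for 30% withdrawal: 83 / (1 − 0.30) = 118.6, so 119 per group and 238 in total; 238 / 6 = 39.7, about 40 per centre. These reproduce. The documents give no AE rate, so all event counts and risks below are assumptions.

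**1. Literal reading, denominator 238.**

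- Arm: 24 subjects with an AE is 24/119 = 20.2%, but 24/238 = 10.1%.
- Centre: 8 subjects of 40 is 20.0%, but 8/238 = 3.4%; the factor is 40/238 = 0.168, about one sixth.
- Comparison, 36 versus 24 subjects: 30.3% versus 20.2% on 119, and 15.1% versus 10.1% on 238. The ratio is 1.5 either way; the difference falls from 10.1 to 5.0 percentage points.

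**2. Arm reading, denominator 119, months 7-12.** Assume a constant AE hazard λ and a constant withdrawal hazard μ over 12 months, with withdrawal unrelated to AE risk and no AEs captured after leaving. Let p be the 12-month risk without withdrawal and w the 12-month withdrawal. Then:

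- Share of AE among exits: λ/(λ+μ) = ln(1−p) / [ln(1−p) + ln(1−w)].
- Incidence among those in study at month 6: I = λ/(λ+μ) × [1 − √((1−p)(1−w))].
- Incidence on all randomised in the arm: √(1−w) × I.

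With p = 0.30 in both arms:

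| w | λ/(λ+μ) | I (at risk) | √(1−w) | On all randomised |
|---|---|---|---|---|
| 0.30 | 0.500 | 15.0% | 0.837 | 12.5% |
| 0.20 | 0.615 | 0.615 × 0.2517 = 15.5% | 0.894 | 13.8% |
| 0.40 | 0.411 | 0.411 × 0.3519 = 14.5% | 0.775 | 11.2% |

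- Equal 30% withdrawal: 12.5% instead of 15.0% in each arm, with no arm difference.
- 20% versus 40%: ratio 1.24 on all randomised and 1.07 on those at risk. Person-time recovers λ = 0.3567/12 = 0.0297 per patient-month in both arms, ratio 1.00.
- Sensitivity: for p from 0.20 to 0.40 the 20%/40% ratio is 1.23 to 1.24. At 10%/50% withdrawal it is 1.54 (1.15 at risk). If all withdrawal fell before month 7 and none after, the 20%/40% ratio would be 0.80/0.60 = 1.33.
- Masking: true risks of 36% versus 30% with 40% versus 20% withdrawal read 13.7% versus 13.8% on all randomised, against 17.7% versus 15.5% at risk.

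**3. Arm reading, whole study.** Incidence is λ/(λ+μ) × [1 − (1−p)(1−w)]. With p = 0.30 it is 25.5% at 30% withdrawal, and 27.1% versus 23.8% (ratio 1.14) at 20% versus 40%. This is the usual crude subject incidence, which also ignores time at risk but to a smaller degree.

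**The case against.** The strongest reply is that the pooled denominator is not established. A table made by arm and centre is naturally read with each column's own population below the line. SAP section 4.6 normally bases percentages on non-missing counts, so section 14 may only mean that all safety subjects are used instead. A separate SAP definitions document, not available here, might settle it. This stands: 238 is one reading of an ambiguous phrase. A reader might infer that the SAP definitely divides every AE rate by 238, or that doing so distorts the arm comparison. The documents do not support either. With 1:1 allocation a common denominator leaves the ratio intact; any false arm difference comes from ignoring time at risk, under either reading.

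Second, no table for months 1-6 and 7-12 is specified; time period appears only in a list of possible breakdowns. That makes the period problem conditional, but the rule names that breakdown and fixes its denominator.

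Third, leaving treatment is not leaving observation. Patients taken off mCR after a reintervention are still tested at 6 and 12 months (protocol section 7.9), and those who leave the study are followed for the events listed in section 7.10. For those events the bias is smaller than calculated. For AEs in general it is not.

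Fourth, the most serious events are covered elsewhere. MACE is analysed by Kaplan-Meier and centre-stratified Cox with censoring (SAP section 8), deaths and SAEs are listed per patient, and section 14 specifies no AE test. This limits the consequence but does not correct the tables. Counting each subject once is also ordinary practice; the gap is only that no event count stands beside it.

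**Conclusion.** The point holds for the descriptive AE tables and should be corrected in the SAP. If the denominator is 238, arm rates and the arm risk difference are halved and centre rates fall to about a sixth. If it is the arm total, whole-study incidence is conventional, but any time-period split is biased downwards because patients who have left remain in the denominator. At the planned 30% withdrawal, spread evenly over 12 months, and an assumed 12-month risk of 30%, months 7-12 read 12.5% instead of 15.0%.

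A false or hidden arm difference requires withdrawal to differ by arm, which the documents neither state nor exclude. The ratio of 1.24 rests on an assumed 20%/40% split; its size depends on that split and on when patients leave. It should not be read as a prediction for this trial, nor as a threat to the MACE analysis or the primary endpoint.

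**What to change.** Replace the denominator sentence in SAP section 14 with a rule on these lines:

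- For whole-study tables, the denominator is the number of safety-population subjects in the arm or centre shown; for the overall column, the whole safety population.
- For any time-period table, it is the number of subjects in that arm still under observation at the start of the period.
- Each table shows the number of events beside the number of subjects with at least one event.
- An exposure-adjusted AE rate, per patient-month of observation, is given by arm, overall and for months 1-6 and 7-12 if a period split is made.

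Both the at-risk denominator and the rate are needed: in the illustration the first still leaves a ratio of 1.07. The cost is a SAP amendment under section 15 and somewhat more table work. It needs AE onset dates and study-exit dates. The protocol describes an AE sheet in the eCRF, and the SAP analyses follow-up time to drop-out, but neither confirms that both dates are recorded, so this should be checked first. No clinical procedure changes.

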## 15. Amendment on the statistical analysis plan

In case of an amendment of the protocol or for other reasons the SAP may be amended accordingly. All amendments will be logged and registered.

Only SAP and "EU-CaRE & EU-CaRE RCT SAP definitions" document with version 1.0 will be approved with a signature of all "authors" and "SC members" as registered on the "signature page" of this SAP.

All *substantial* changes of both documents after initial approved version 1.0 need approval from the "authors". A substantial change is marked via a full upgrade of the version number (e.g. 2.0 to 3.0 or 2.1 to 3.1) of the related document.

All *non-substantial* changes after initial approved version 1.0 only need approval from the "authors" of coordinating partner Diagram. A non-substantial change is marked via a partly upgrade of the version number (e.g. 2.0 to 2.1 or 3.1 to 3.2) of the related document.

[figure not shown]

## **16. Conduct of statistical analysis**

All statistical calculations will be performed using SAS version 9.3 or higher, SPSS version 19 and R version 3.3.1., R Core Team (2016). Statistical analysis will be performed by the beneficiaries Bern, Santiago, Ludwigshafen, Copenhagen and CRO Diagram. Diagram will have an overview of all analyses that will be performed.

Diagram, as reviewing party, will independently reproduce the primary analyses and summary statistics table X, Y, Z. Diagram will explicitly check the code producing tables A, B & C (selected at random) as well as other pieces of code as desired. Each beneficiary is responsible for quality control of all macros and programs used during the analysis.

[figure not shown]

## 17. Reporting conventions

The following reporting conventions will be applied. P-values  $\geq 0.001$  will be reported to 3 decimal places. P values less than 0.001 will be reported as "< 0.001". The mean, standard deviation, and any statistics other than quantiles, will be reported to one decimal place greater than the original data. Quantiles, such as median, or minimum and maximum will use the same number of decimal places as the original data. Estimated parameters, not on the same scale as raw observations (e.g. regression coefficients) will be reported to 3 significant digits.

[figure not shown]

## 18. Summary of changes to the protocol

A per protocol analysis set is added to the SAP. Analysis for primary and secondary endpoints will be repeated for the per protocol population. In the per protocol analysis population we will take into account the subjects who adhere to the protocol in terms of subjects who adhere to the major criteria in the protocol and who have a cardiopulmonary exercise test (CPET) test with sufficient quality of tests at T0, T1 and T2. For the intervention group this implies subjects who complied with the use of the smartphone (use of the smartphone on at least 4 days per week with a minimum of 30 minutes of activity per day with a total registration of 150 minutes of activity per week during 21 weeks) during the first 6 months of the study. The per-protocol restricts the comparison of the treatments to the ideal patients, that is, those who adhered perfectly to the clinical trial instructions as stipulated in the protocol. A per-protocol analysis answers the questions as to whether the treatment works among those that comply, but it can never provide an unbiased assessment of the true effect since the decision to comply with a treatment is unlikely to occur at random. Both will be used as supportive analysis.
